**Figure 1 figure1:**
[figure not shown]
Person-centered narrative intervention (PCNI) workflow figure. EHR: electronic health record.

#### Outcome Evaluations of the PCNI

##### Usability Testing

Using a human, organization, and technology–fit factor [53] evaluation framework for health information systems, we will collect data across several usability factors. Usability is defined as the relationship between humans and computers [53]. Usability testing [53,56,57,60] focuses on evaluating process measures based on 4 major components: user (clinician), task (use of metanarrative), system (metanarrative in EHR), and environment (outpatient setting). This user-task-system-environment framework of process measures [61] will be incorporated into our usability testing to determine barriers and facilitators from the clinician’s perspective, and to help determine the essential requirements for integrating the narrative intervention into the EHR by evaluating information flow, use of information, and system functionality. The process measures collected to determine usability will include (1) chart review and log analysis of the clinical use of the patient’s story; (2) time and cost analyses of collecting the story, writing and cocreating the metanarrative, and uploading the final metanarrative into the EHR; and (3) exit surveys and interviews with both patient and clinician participants.

##### Intervention Uptake and Attrition

We will also analyze the intervention uptake and attrition between baseline and follow-up data collection points [47-49]. Uptake (acceptability) will be assessed using descriptive summaries examining acceptors among people approached for recruitment. The number of dropouts, reasons given, and the timing of withdrawals from the study will also be reported. When possible, patient participants who drop out will be provided with a 1-page query about why they left the study. Feasibility will be examined by examining operational issues, namely, staff time spent or issues with recruitment, EHR use, or training. Identified issues will be noted in project logs to guide future studies. These are critical steps for evaluating scalability for the successful implementation of PCNIs in other complex systems. This approach incorporates the human, organization, and technology–fit [53] factors for the successful implementation of PCNIs.

#### Patient-Reported Outcomes

The primary patient-reported outcome measures for this protocol are the PROMIS (patient-reported outcomes measurement information system)-29 Profile v2.0 form [62] and PROMIS Psychosocial Illness Impact [63]. The PROMIS-29 profile v2.0 form consists of 29 items that assess physiological, social, and psychological outcomes. These biopsychosocial domains include physical function, anxiety, depression, fatigue, sleep, the ability to participate in social roles or activities, and pain interference and intensity. The PROMIS Psychosocial Illness Impact measure consists of 16 items that assess the negative and positive aspects of the illness experience. The PROMIS positive item bank measure (8 items) assesses the positive psychosocial outcomes of illness. Positive psychosocial illness impacts refer to outcomes, such as greater life appreciation, interpersonal relationships, and personal resources, that can occur because of confrontation with one’s mortality. The PROMIS negative item bank measure (8 items) assesses the direct negative psychosocial effect of illness, distinct from general emotional distress. All PROMIS measures have established reliability and validity. At baseline, demographic information will also be collected from patient participants, including age, biological sex, gender, race and ethnicity, perceived illness severity, years of education, income, marital status, religion or spirituality preference, and clinical details (to identify comorbidities and severity of illness).

The primary outcome measures for the patient participants will be collected across 3 time points. After enrollment, the research team will generate participant-specific survey links in REDCap [46] and email them to the participants to complete the demographic survey and the baseline (time point 1) outcome measures (Table 1). Outcome measures could also be collected by phone, if preferred by the participant. At a mutually scheduled time, the participant and a research team member will meet on a secure videoconference to conduct and audio record the PCNI interview, as described previously in *The PCNI Procedure*. Within 48 hours after the narrative is uploaded into the EHR, participants will complete time point 2 outcome measures using the same process described for time point 1. Time point 3 will be completed 1 month after the narrative upload and the NPV. Finally, after time point 3, the research team will conduct exit interviews with patient participants at the end of their study participation to collect information about their experience, including suggestions for improvement (Textbox 1 lists the interview questions).

For the clinician participants, the research team will conduct exit interviews with clinician participants within 2 to 4 weeks of their initial appointment with a patient participant to collect information about their experience of having and using the patient narrative before the initial consult. At the end of study enrollment, 1 to 2 audio-recorded focus groups (based on scheduling needs) will be cofacilitated by research team members with all the clinician participants to collect additional information and feedback about their experience and facilitate and record group discussion about their use of the patient narratives in their clinical practice. Interviews will be conducted via a secure videoconference or a phone call and audio recorded. See Table 1 for participant study activities.

**Table 1 table1:** Participant study activities.

Participant	Outcome	T1: baseline (prenarrative upload)	T2: 24-48 hours after T1 (postnarrative upload to EHR^a^)	T3: 1 month after T1
Patient	Biopsychosocial and spiritual well-being	PROMIS^b^-29-Profile PROMIS Psychosocial Illness Impact; positive and negative effects	PROMIS-29-Profile PROMIS Psychosocial Illness Impact; positive and negative effects	PROMIS-29-Profile PROMIS Psychosocial Illness Impact; positive and negative effects
Patient clinician	N/A^c^	N/A	N/A	Exit interviews

^a^EHR: electronic health record.

^b^PROMIS: patient-reported outcomes measurement information system.

^c^N/A: not applicable.

### Data Analysis

#### Quantitative Analysis

Analyses will be performed using SAS software (version 9.4; SAS Institute Inc) [64]. Analyses will be primarily descriptive to determine the feasibility of collecting patient-reported outcome data in this setting (ie, data completeness) and summary statistics and distributional characteristics of those outcomes. Data will be inspected for errors and outliers. Data completeness will be summarized in terms of missing responses across the 3 data collection time points (ie, percent attrition at each follow-up) as well as missing item responses within each measurement period (ie, inspection of item-level missing data patterns). A high level of retention (>90%) across follow-up waves is expected based on previous research in an inpatient setting [14]; however, this will be empirically investigated. Missing responses at the item level are similarly expected to be low, but if present, they will provide information on potential response fatigue or problematic items. Baseline demographics and outcome measures at all 3 waves will be summarized using standard descriptive statistics (eg, mean, SD, and range). Preliminary testing of the outcome measures for change from baseline, T2, and T3 will be analyzed in a repeated measures framework (time effect in mixed effect model) to evaluate the effects of the intervention on the individual patient participant’s patient-reported outcomes of the PROMIS 29 Profile and PROMIS Psychosocial Illness Impact. This single-arm study is not powered to evaluate the statistical significance of changes in patient-reported outcomes over time; however, distributional characteristics of outcomes and effect size estimates of mean change will be useful for informing a larger-scale randomized trial.

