**Methods:**

Using a mixed method design, this single-arm intervention feasibility study was delivered over approximately 3 to 4 weeks. Patient participant recruitment was conducted via screening outpatient palliative care clinic schedules weekly for upcoming new palliative care patient visits and then emailing potential patient participants to notify them about the study. The PCNI was delivered via email and Zoom app. Patient-reported outcome measures were completed by patient participants at baseline, 24 to 48 hours after PCNI, and after the initial palliative care clinic visit, approximately 1 month after baseline. Inclusion criteria included having the capacity to give consent and having an upcoming initial outpatient palliative care clinic visit.

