## Introduction

### Background and Rationale

Health care advances have extended the life span and cured many diseases; however, advanced health care treatments are sometimes discordant with patient preferences, values, and beliefs, which can lead to insufficient symptom control, difficult patient-clinician interactions, and poor psychosocial and spiritual support [1-3]. Furthermore, poor patient-clinician communication contributes to continued unwanted care. A comprehensive palliative care approach improves communication, leading to better quality of life (QoL) for patients [4-6]; however, discordant care continues in part because of knowledge gaps about patients’ psychological, social, and spiritual needs [7-10]. Person-centered narrative interventions (PCNIs) can fill these knowledge gaps [11-20], yielding an increased understanding of patients’ psychological, social, and spiritual needs, which will help clinicians develop tailored palliative care interventions.

Storytelling (narrative) is an effective way for patients to communicate their cultural values and beliefs. As early as 1542, when Joannes Fernel coined the term physiology, the discussion at that time described the person as a structure of physiological, pathological, and clinical stories [21]. However, in the health care system, patients do not always have the opportunity to share their clinical stories with their clinicians [3,22-26]. Furthermore, even if patients have the opportunity to discuss values, beliefs, and preferences for care, some research has described treatment errors that may occur when clinicians overlook contextual information in a clinic visit. These treatment errors are known as contextual errors [27-29] and are defined as a “decision making error that occurs because of inattention to patient context” [29].

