
### Objectives

In this protocol, we aim to further develop the continued testing of the feasibility and efficacy of the EHR integration of PCNI in an outpatient setting using an all-internet-based–delivered platform. The first objective of this study is to identify barriers and facilitators of an internet-based–delivered PCNI from the perspectives of persons living with serious illness and their clinicians. The second objective is to conduct acceptability, usability, and intervention fidelity testing to determine the essential requirements for the EHR integration of an internet-based–delivered PCNI. The third objective is to test the feasibility of the PCNI in an outpatient clinic setting.

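### The single-arm time effect is to be read as an effect of the intervention, although by the text T3 follows the first palliative care visit

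*Protocol article*

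**What the plan says.** The Abstract describes the design: "this single-arm intervention feasibility study was delivered over approximately 3 to 4 weeks". There is no comparison group. All patients are newly establishing care at an outpatient palliative care clinic (Participants).

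The Quantitative Analysis section analyses change in the PROMIS measures across baseline, T2 and T3 in a "repeated measures framework (time effect in mixed effect model"). It gives the purpose as "to evaluate the effects of the intervention on the individual patient" participant's outcomes. It calls the analyses mainly descriptive and this step preliminary, and says the study lacks power to test change over time. It then says that effect sizes for mean change will help to plan a larger randomized trial.

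On timing, the Patient-Reported Outcomes section says: "Time point 3 will be completed 1 month after the narrative upload and the NPV". The Abstract places the last assessment "after the initial palliative care clinic visit, approximately 1 month after baseline". The Objectives section speaks of "continued testing of the feasibility and efficacy of the EHR integration of PCNI in an outpatient setting".

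The Limitations list the single location and health system and the need for email and internet access. They do not mention the lack of a control or the visit that falls before T3.

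**The concern.** In one arm, a time effect estimates change from all causes. The plan assigns that change to the PCNI. Yet the design places another active component, the first specialist palliative care visit, before the last assessment. The Background itself says of such care: "A comprehensive palliative care approach improves communication, leading to better quality of life (QoL) for patients". On the protocol's own premise, PROMIS scores could improve by T3 with no PCNI effect. They could also worsen with the illness and hide a real benefit.

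Two things are at stake. One is what the study may conclude about patient-reported outcomes. The other is the number handed to the randomized trial: if both arms of that trial receive the palliative care visit, the T1-T3 change in this study is not the between-arm difference the trial will estimate. More patients would not help, because the problem is bias and not imprecision.

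**Working it through.** The plan states no alpha, effect size, SD or power, and N=20 is justified by qualitative and usability methods. There is no figure to reproduce. The check therefore has three parts: what each contrast contains, when T2 and T3 fall, and an illustration of size.

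**1. What each contrast contains**

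| Contrast | PCNI component | Other contributions |
|---|---|---|
| T1-T2 | Interview, cocreation and upload | Time, illness course, regression to the mean |
| T1-T3 | The same, plus the clinician's use of the narrative at the visit | The same over a longer period, plus the first palliative care visit itself |

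Regression to the mean is possible rather than shown: entry does not depend on a PROMIS score, but patients may reach palliative care at a bad time.

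**2. When T2 and T3 fall**

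- T3: about one month after baseline and after the visit (Abstract); one month after the upload and the visit (Patient-Reported Outcomes); one month after T1, with no mention of the visit (Table 1).
- Patients are contacted about 4 weeks before the visit (Participants). Let T1 fall x days after contact and take one month as 30 days (assumption). On Table 1's schedule, T3 falls at -28 + x + 30 = x + 2 days after the visit: 2 days for x=0, 9 for x=7, 16 for x=14. One month after the visit would be day 30. Exposure to palliative care by T3 therefore differs widely between the definitions. At x near 0 the approximate dates could put T3 close to the visit.
- T2: 24 to 48 hours after the PCNI (Abstract); within 48 hours of the upload (text); 24 to 48 hours after T1, yet also after upload (Table 1). The Discussion reports that member checking alone averaged 5 days, and it comes between T1 and upload. Table 1's interval does not fit that.

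**3. Size, as an illustration**

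Inputs: n=20 (Participants), and n=18, which is 90% of 20 (expected retention is above 90%). Assumed: a two-sided paired t-test at alpha 0.05, PCNI effect zero, and a background shift of d SDs of the change score. With critical value t = 2.093 (19 df) or 2.110 (17 df),

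P(significant) = 1 - F(t; n-1, d√n) + F(-t; n-1, d√n), where F is the noncentral t distribution function.

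| Background shift d | n=20 | n=18 |
|---|---|---|
| 0.2 | 0.14 | 0.13 |
| 0.3 | 0.25 | 0.23 |
| 0.5 | 0.57 | 0.52 |
| 0.8 | 0.92 | 0.89 |

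The nominal rate is 0.05. The 95% confidence interval half-width is t/√n: 2.093/√20 = 0.47 and 2.110/√18 = 0.50 SDs of change. A larger n narrows the interval around the combined change and leaves the bias unchanged.

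For the randomized trial, sample size scales with 1/d². If the PCNI accounts for a fraction f of the observed change (assumption), a trial sized on the whole change needs 1/f² times as many patients as planned: 1.8 times for f=0.75, 4 times for f=0.5, 16 times for f=0.25.

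**The case against.** The plan is cautious in most respects. It calls the analysis mainly descriptive and preliminary, names the study as single-arm, disclaims power, and leaves controlled testing to a later trial. No decision rule depends on the time effect. The initial findings in the Results claim only that the PCNI was feasible, acceptable and usable. The Background sentence concerns palliative care in general, not the effect of one visit on PROMIS. All of this stands, and it lowers the severity. It does not answer the point: the caveats concern precision, while the sentence that gives the model its purpose concerns attribution.

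A reader might infer more than the documents support:

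- **That confounding is complete in every patient.** The Discussion reports one patient whose narrative was not uploaded before the visit, so that patient's T2, if taken after upload, also followed it. Table 1's T3 could fall close to the visit.
- **That T1-T2 is the only contrast relevant to the PCNI.** The narrative is uploaded for the clinician to use at the first consultation, and the central hypothesis includes better communication and care. That pathway acts at or after the visit, so T1-T2 would miss it. T1-T2 is also uncontrolled.
- **That PROMIS is wrongly called primary.** The section says "The primary outcome measures for the patient participants will be collected across 3 time points", but this follows a sentence naming them primary among patient-reported measures, and the Abstract's aim includes effects on such outcomes. Relabelling them exploratory would be a preference.
- **That multiple testing over the PROMIS scores shows the size of the problem.** The documents state no significance rule, the scores are unlikely to be independent, and multiplicity does not measure confounding.

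**Conclusion.** The point holds at moderate severity. As written, the plan reads an uncontrolled time effect as an effect of the intervention and offers it for planning a trial. By the text and the Abstract, the T1-T3 change includes the first palliative care visit. The T1-T2 change normally precedes that visit but is uncontrolled too.

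The size and direction of the bias cannot be obtained from the documents. The probabilities above rest on an assumed alpha and assumed background shifts. They show only that an ordinary shift could produce an apparent effect at this sample size. The conclusion does not depend on which T3 definition applies, since none supplies a control; the definition affects how much palliative care T3 reflects. A reader might also conclude that the study will report efficacy. The documents do not show this, and the wording is the only basis for the worry.

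**What to change.** 1. In Quantitative Analysis, replace the stated purpose of evaluating intervention effects with describing uncontrolled within-patient change over time.
2. Report T1-T2 and T1-T3 separately as estimates with 95% confidence intervals, both marked as uncontrolled, and label T1-T3 as including the first palliative care visit.
3. Do not pass the T1-T3 mean change to the randomized trial as a PCNI effect size. The SDs, within-patient correlations and data completeness remain usable for planning.
4. Remove efficacy from the aim in the Objectives section.
5. Add the missing control and the intervening visit to the Limitations.
6. Reconcile the T2 and T3 timing in Table 1 with the Abstract and the Patient-Reported Outcomes text.

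The cost is wording and two reported contrasts from data already collected. The drawback is a weaker claim about patient-reported outcomes.

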## Methods

### Study Design

This study will use a mixed methods design [41,43-45] and collect data from both patient and clinician participants. Our study relies on the CFIR [41,45] to inform the implementation of this single-arm trial across the 2 years of the study. This is a novel approach that documents what affects implementation in a new context of outpatient clinical care with a protocol that is all delivered electronically. The CFIR is a conceptual framework developed to guide multilevel assessment of factors that may influence an intervention’s implementation and effectiveness [41,45]. The core CFIR domains are (1) intervention characteristics, (2) inner setting (ie, implementing organization), (3) outer setting (ie, external environment), (4) individual characteristics (ie, knowledge and beliefs of the individuals involved in the implementation), and (5) processes (ie, strategies and tactics used in the implementation [41,45]). Within each domain, specific constructs may influence the implementation. Constructs in the proposed taxonomy of implementation outcomes have the potential to capture clinician attitudes (acceptability) and behaviors (adoption and uptake) as well as contextual factors (system penetration, appropriateness, and implementation).

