### Participants

Purposeful sampling strategies will be used to recruit and enroll 20 patients. The small sample size was chosen to be consistent with both qualitative data analysis techniques [50] and usability data analysis techniques [56,57]. Patient participants (N=20) who are aged ≥18 years (no upper limit), able to read and speak English, and capable of providing informed consent will be enrolled in the study. Owing to the feasibility of this study, we allowed participants to enroll at any stage of illness or symptom acuity. These participants will be newly establishing care at one of the University of Colorado Hospital (UCHealth) outpatient palliative care clinics (Outpatient Palliative Care Clinic and Supportive and Neuro-Palliative Medicine Clinic). The clinician participants (N=10) will be members of the outpatient palliative care interprofessional team, which includes physicians, advanced practice clinicians, registered clinicians, social workers, and a spiritual care clinician. These clinician participants will be included if they are able to confirm verbally that they were involved in the outpatient palliative care of a patient participant.

For the patient participants, the research team will review the outpatient palliative care clinic schedules weekly via the EHR (Epic) to identify persons with upcoming initial new patient visits (NPVs) in the palliative care clinics. These identified persons will receive an initial recruitment email with an institutional review board–approved language and a follow-up email with the initial language approximately 1 week later for those who have not responded. For those who respond to the recruitment email with interest, the research team will arrange a secure videoconference or phone call to discuss the study, review the consent form, and answer questions. When a person opts to participate, the research team will send an email with a link to the electronic consent form (in REDCap) [46] and instructions for completing the consent. It should be noted that persons are contacted approximately 4 weeks before their NPV to facilitate ample time for pre-NPV study activities.

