
## Results

The study received funding in January 2021, and ethics approval was received on March 21, 2021. The recruitment of participants began in April 2021. Patient participant recruitment was conducted via weekly screening of the outpatient palliative care clinic schedules for upcoming new palliative care patient visits, and emails were sent to potential patient participants. At this time, some data have been collected and analyzed. A total of 189 potential patient participants were approached via email, and 20 patient participants were enrolled, with data having been collected from May 2021 to September 2022. A total of 7 clinician participants were enrolled, with a total of 3 clinician exit interviews conducted in 2021 and 2022 and 1 focus group (n=5) conducted in October of 2022. Data analysis has been ongoing from the end of data collection in October 2022 to June 2023. Overall, for this feasibility study, we were able to recruit a total of 20 patient participants and 7 clinician participants for data collection. In the initial findings, the electronically delivered person-centered narrative was feasible, acceptable, and usable for both patient and clinician participants. The overall findings are expected to be submitted for publication by the end of June 2023.

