In the last CFIR domain of process, we implemented several strategies and tactics for the successful implementation. As we began email recruitment and electronic consenting, we chose not to enroll any patient participant who was noted to have a medical diagnosis of Alzheimer disease or dementia, or terms of cognitive impairment, confusion, or delirium on their problem lists. For this study, this screening excluded 20% of persons with a new patient palliative care visit. At this stage of data analysis, we would suggest that future PCNI programs should consider cognitive impairment. In future studies, the need for a mental capacity screening can be an important consideration. Alternatively, in future studies, the PCNI would need to consider the cognitive capacity of persons who have a serious illness and include a person’s support individuals to be a part of a dyadic PCNI. It should be noted that the integration of the PCNI into an outpatient palliative care clinic provides systematically more time for palliative care clinicians to engage with the narrative based on the allowed new palliative care patient visit time allotment of 1 hour. In future studies in other clinical settings that are nonpalliative, the acceptability and usability of the person’s narrative will require clinical workflow evaluations of the best strategies for allowing the nonpalliative clinician adequate time to engage with the person’s narrative. As in our other PCNI studies, once a patient participant is enrolled, there are limited withdrawals. Only 1 participant reported mild distress with the narrative interview questions that were being asked and made a choice to withdraw from the study.

Finally, although the overall goal of the PCNI is to consider the improvement of the quality of communication in clinical care, for this protocol, the quality of communication is being analyzed by exit interviews with both patient and clinician participants. In our other PCNI study [14], the quality of communication measure has been used [65]. However, in this study, the patient participants were enrolled before NPVs with the palliative clinical team. Therefore, we were unable to quantitatively measure any changes in the quality of communication between the patients and palliative care clinicians. For future studies of PCNIs, the consideration of not timing the PCNI before an NPV should be considered.

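### The uncontrolled change over time is read as the effect of the intervention and offered to inform a randomized trial, but it is not a between-arm difference and is imprecise with 18 to 20 patients

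*Protocol article*

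**What the plan says.** The Study Design section describes a single-arm trial. The Participants section states: "Purposeful sampling strategies will be used to recruit and enroll 20 patients". It justifies that number by what is usual for qualitative and usability analysis, not by precision or power. The Results section confirms it: "A total of 189 potential patient participants were approached via email, and 20 patient participants were enrolled".

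The Quantitative Analysis section calls the analyses mainly descriptive. For the two PROMIS instruments it plans a "repeated measures framework (time effect in mixed effect model) to evaluate the effects of the intervention" on patient-reported outcomes at baseline, T2 and T3. It then concedes that the study is not powered for the statistical significance of change over time. The same sentence goes on to say that distributional characteristics and "effect size estimates of mean change will be useful for informing a larger-scale randomized trial".

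On timing, the Patient-Reported Outcomes section places T2 within 48 hours after the narrative is uploaded to the health record, and T3 after both the upload and the new patient visit. The Discussion (Overview) reports that upload came before the initial visit in all patients but one. The Limitations section names the single site and health system and the need for email and internet access. It does not mention the absence of a control arm.

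**The concern.** Two steps in the plan go further than the design allows. First, a time effect in one arm is change over time, and it equals the effect of the intervention only if nothing else would have moved the scores. Here the first palliative care visit falls before T3, and the Background and Rationale section itself credits a comprehensive palliative care approach with better quality of life. The article thus names a rival cause of improvement in its own outcome domain, one that a control arm in the same clinics would share.

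Second, the effect size of that change is put forward as useful for a randomized trial, with no statement of what it may be used for. The most obvious use of an effect size in planning a trial is as the expected or target difference. Taken that way, this number would be both the wrong quantity and a very imprecise one.

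**Working it through.** The article derives no sample size, power or precision figure for the patient-reported outcomes, so there is no stated figure to reproduce. The check asks what about 20 patients can say about a mean change.

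**Inputs from the article**
- n = 20 enrolled (Participants; Results).
- Retention is expected to exceed 90% (Quantitative Analysis). The boundary is 0.90 × 20 = 18, so n = 18 to 20 is used. One withdrawal is described (Discussion, Overview), which would leave 19.

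**Assumptions, because the article gives none**
- The effect size is mean change divided by the SD of change.
- Observed values of 0.3, 0.5 and 0.8.
- Within-patient correlation of 0.3 to 0.8.
- For illustration of a later trial: two-sided 5%, 80% power, 1:1 allocation.

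**Step 1. Precision of the mean change**, in SD-of-change units. Half-width = t(0.975, n-1)/√n.
- n = 20: 2.093/4.472 = 0.47
- n = 19: 2.101/4.359 = 0.48
- n = 18: 2.110/4.243 = 0.50

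**Step 2. Exact interval for the standardized change** (noncentral t, with t = d√n).

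| Observed d | 95% CI, n = 20 | 95% CI, n = 18 |
|---|---|---|
| 0.3 | -0.15 to 0.74 | -0.18 to 0.77 |
| 0.5 | 0.03 to 0.96 | 0.00 to 0.98 |
| 0.8 | 0.29 to 1.30 | 0.26 to 1.32 |

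For an observed 0.3 the interval includes zero. For 0.5 it runs from almost nothing to large. Only for a large observed change does the lower limit move well clear of zero.

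**Step 3. What this would mean if the number were taken as a between-arm effect.** Patients per arm = 2(1.960 + 0.842)²/d² = 15.70/d².
- Observed 0.5: 15.70/0.25 = 62.8, so 63 per arm. The upper limit (0.96) gives 18 and the lower limit (0.028 before rounding) gives about 19,500.
- Observed 0.8: 25 per arm, with 10 to 192 over the interval.
- Observed 0.3: 175 per arm at the point estimate. The interval includes zero, so there is no upper bound.

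**Step 4. Within-group change against between-arm difference.** Suppose a share s of an observed 0.5 would also occur in a control arm. The between-arm effect is then 0.5(1 - s). The share is unknown, so a range is shown.

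| s | Between-arm effect | Needed per arm | Power with 63 per arm |
|---|---|---|---|
| 0 | 0.500 | 63 | 80% |
| 0.25 | 0.375 | 112 | 56% |
| 0.50 | 0.250 | 252 | 29% |
| 0.75 | 0.125 | 1,005 | 10% |

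**Step 5. Scale.** If the standardizer is the SD of change, and the SD is the same at both time points, then change in baseline-SD units = d × √(2(1 - r)). For d = 0.5 this is 0.59 at r = 0.3 and 0.32 at r = 0.8, or 45 and 157 per arm. The same reported figure means different things until its denominator is stated.

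**Step 6. What the study can pass on.** An outcome SD from 20 patients has a 95% CI from 0.76 to 1.46 times its estimate (√(19/32.85) and √(19/8.91)). That is usable for planning if its interval is carried along.

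**The case against.** The strongest reply is that the article claims little. It calls the analyses mainly descriptive, admits it is not powered for change over time, lists distributional characteristics alongside the effect sizes, and speaks of informing a trial. It already plans means, SDs, ranges, attrition and item-level missingness. It also cites earlier acute-care work and an ongoing pilot, so nothing shows that this study would be the only input. Nothing in the present study turns on the clause.

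Much of this stands, and it limits the point. A reader might infer four stronger things that the documents do not support:
- **That a future trial will be sized on this number.** Sizing is not stated. Steps 3 and 4 show only what such a use would entail, with assumed effects and shares.
- **That all change is confounded by the palliative care visit.** That holds for T3. T2 generally precedes the visit.
- **That regression to the mean inflates the change.** It cannot be shown. Patients were not selected on a baseline score, and enrolment was open to any illness stage or symptom acuity.
- **That the absence of a planned confidence interval, or of a defined standardizer, is an error in itself.** A condensed article may leave both to the full protocol or analysis plan.

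The core is not answered. The power caveat covers statistical significance only, and the sentence then turns to endorse the effect sizes. The time effect is still described as evaluating the intervention, and the Limitations section does not correct that.

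**Conclusion.** The point holds in limited form. The article gives an uncontrolled within-group change a meaning (the effect of the intervention) and a use (informing a randomized trial) that a single-arm design cannot support without qualification. The T1 to T3 change combines the narrative with the first palliative care visit and the course of illness. The T1 to T2 change is mostly free of the visit but is still uncontrolled.

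On size, the uncertainty of about half an SD either way is enough that a small or moderate observed change cannot fix a target difference. A large one would be distinguishable from zero but would still not be a between-arm effect. The precision figures rest on 18 to 20 patients with follow-up and on standardizing by the SD of change. That a within-group change is not a between-arm difference rests on neither. Correction is worthwhile because analysis was still under way when the article was written, and the wording would carry into the results paper and the next protocol.

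**What to change.** Make three changes in the Quantitative Analysis section:

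1. Describe the time effect in the mixed model as change over time in patient-reported outcomes, not as the effect of the intervention.
2. Report mean change at T2 and T3 with its 95% CI, as descriptive only, and state the denominator if it is standardized.
3. Replace the clause on effect sizes with wording such as: outcome SDs with their 95% CIs, within-patient correlations between time points, retention and data completeness will inform a randomized trial; the mean change observed here will not be used as its expected between-arm effect.

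A sentence in the Limitations section noting that there is no control arm, and that the first palliative care visit precedes T3, would complete it.

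The cost is a few sentences and interval output from the model already planned, with no new data. The downside is that the study claims slightly less about preliminary effect.
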